Assessed for eligibility with inclusion and exclusion criteria

Obtaining written consent

Randomized with computer program by an independent statistician and the allocation sequence will be concealed with sealed and stapled opaque envelopes

Baseline assessment

G2

DN with placebo US-guide+

supervised exercise, exercise pamphlet and educational video

G1

DN + real US-guide+ routine supervised exercise and exercise pamphlet, educational video

G3

Control from waiting list without any treatment

Follow up immediate after the last session at the 4-week and 8-week follow-ups, and data analysis and post intervention analysis with mixed model ANOVA

1. Sample Size and rational for calculation

The effect size is calculated by using G-Power version 3.1.9.4 (Franz Faul, Universität Kiel, Germany)

With reference previous similar study of using acupuncture on KOA (Williamson et al., 2007), the effect size of VAS is set as 0.339 for the VAS, power as 0.8, level of statistical significance as 0.05. The number of subjects estimated for each group will be 26; total number of subjects was 78.

1. Method of data analysis:

Statistical analyses will be performed on the Intention to treat (ITT) population, including all randomized participants. Missing data will be replaced using multiple imputation (5 iterations). Intention to treat (ITT) analysis will be used in the data analysis. The data will be analyzed by using mixed model analysis of variance (ANOVA) (two-tailed) with ‘time’ as the within subjects factor (Baseline, 4 weeks and 8 weeks after treatment), whereas the ‘group’ factor will be analyzed for the between groups differences (G1, G2 and G3). The significant level will be set at 0.05 and bonferroni correction will be applied. Wilks’ Lambda will be used for statistic significance analysis. The assumption of sphericity will be tested by the Mauchly’s test and the assumption of normality will be tested by the Shapiro-Wilk test. Post hoc analysis by will be conducted if significant difference is found in the corresponding outcomes measures so as to identify the difference amongst the comparisons between groups. All statistical analysis will be conducted using SPSS version 23 (IMB, SPSS) and all analyses will be processed blind to identify of treatment groups by an independent research assistant.

1. Details of procedure of applying US-guided DN

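### The plan compares the groups through a factor that includes baseline, never names group-by-time as the test, and does not adjust for baseline

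*Protocol*

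**What the plan says.** The Methodology section of the protocol, under the method of data analysis, plans a "mixed model analysis of variance (ANOVA) (two-tailed") with time "as the within subjects factor (Baseline, 4 weeks and 8 weeks after treatment"). Baseline is therefore one of three outcome levels. The group "factor will be analyzed for the between groups differences (G1, G2 and G3"). Post hoc comparisons between groups follow a significant result, with no visit named.

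The same paragraph says that Wilks' "Lambda will be used for statistic significance analysis" and plans Mauchly's test of sphericity. It also states that "The significant level will be set at 0.05 and bonferroni correction will be applied" and that "Missing data will be replaced using multiple imputation (5 iterations"), in an intention-to-treat population of all randomised participants.

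It names no group-by-time interaction, no change score and no baseline covariate, although VAS and KOOS are measured at baseline in every group.

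**The concern.** The two null hypotheses concern differences among the three groups in pain and in function. The only term that the plan ties to such differences is the group factor. In a mixed ANOVA with baseline as a level of time, the group main effect averages each arm over all three visits. Baseline precedes treatment, so in randomised arms its expected difference is zero, and including it pulls the estimated difference towards zero.

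The Wilks and Mauchly sentences point to a different term. The main effect and the interaction give different tests and different estimates, and the plan does not say which decides the hypotheses, so the choice could be made after the data are seen. On either reading, baseline is spent as an outcome when it could serve as a covariate that removes variance.

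**Working it through.** **Inputs from the protocol.** Three time levels; the group factor as the named comparison; 30 per group, N=90; calculated size 26 per group, N=78; and "the effect size of VAS is set as 0.339 for the VAS, power as 0.8, level of statistical significance as 0.05".

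**Assumptions, not in the protocol.** 0.339 is Cohen's f and applies at both 4 and 8 weeks; SD is 1 at each visit; every pair of visits has the same correlation rho (0.3, 0.5 or 0.7); data are complete; alpha is 0.05 before any Bonferroni correction.

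**The stated sample size.** A one-way ANOVA with noncentrality f²N has power 75.1% at N=78 and needs N=87 for 80%. A repeated-measures between-factor test on three measurements, with noncentrality 3f²N/(1+2rho), needs N=60 at rho=0.5 and gives 78 only for rho of about 0.79 to 0.84. The protocol states neither the test family nor the correlation, so 78 cannot be confirmed. The steps below do not depend on it.

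**Step 1: what the main effect estimates.** Let d4 and d8 be the true differences between two arms at 4 and 8 weeks.
- Group main effect: (0 + d4 + d8)/3
- Average post-baseline difference: (d4 + d8)/2
- Ratio: (1/3)/(1/2) = 2/3, whatever the correlation.

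To show the scale only: a constant difference of 19.9 mm on the VAS gives 19.9 × 2/3 = 13.3 mm. Against a single visit, the shrinkage is one third only if d4 = d8; if d8 = 0, the main effect is d4/3.

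**Step 2: variances.**
- Mean of three visits: (1+2rho)/3 = 0.533 / 0.667 / 0.800
- Mean of weeks 4 and 8, adjusted for baseline: (1+rho)/2 − rho² = 0.56 / 0.50 / 0.36
- One visit, adjusted for baseline: 1 − rho² = 0.91 / 0.75 / 0.51

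**Step 3: power.** The noncentrality is Nf² × (scale factor)²/variance, where Nf² = 90 × 0.339² = 10.34. The scale factor is 2/3 for the main effect and 1 for the adjusted analyses. At rho=0.5:
- Main effect: 10.34 × 0.444/0.667 = 6.90, F(2,87)
- Adjusted, one visit: 10.34/0.75 = 13.79, F(2,86)
- Adjusted, mean of two visits: 10.34/0.50 = 20.69, F(2,86)

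The Wilks interaction test was simulated under the same model.

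| Test, N=90 | rho 0.3 | rho 0.5 | rho 0.7 |
|---|---|---|---|
| Group main effect, baseline as a level | 74% | 63% | 55% |
| Wilks group-by-time | about 69% | about 84% | about 98% |
| ANCOVA, one visit | 85% | 91% | 98% |
| ANCOVA, mean of weeks 4 and 8 | 97% | 98.5% | 99.8% |

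At N=78 the main effect has 67 / 56 / 49%, the Wilks interaction about 61 / 77 / 95%, and ANCOVA on the two-visit mean 95 / 97 / 99.5%.

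**The case against.** The strongest reply is that the plan already intends a group-by-time test. With one outcome measured three times, Wilks' Lambda and Mauchly's test apply to the within-subject terms; the group main effect needs neither. The clause about the group factor can be read as the layout of the model, and both hypotheses speak of modulation, which suits a test of change. On that reading nothing is shrunk, and power at N=90 exceeds the planned 80% at rho 0.5 and 0.7. At rho 0.7 the gain from baseline adjustment is negligible. This stands: the interaction is a fair inference. It remains an inference, because no sentence names it as the test of the hypotheses.

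The power figures also depend on inputs that the protocol lacks. If 0.339 were the effect size of the repeated-measures between factor itself, the main effect would have 98 / 94 / 90% power at N=90. And the two-visit mean is the most favourable comparator: at one visit and rho 0.5, the gain over Wilks is 91% against about 84%. Both reservations stand. They affect the size of the loss under the literal reading, and leave the two-thirds ratio untouched.

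A reader might go further in three ways that the document does not support:
- That every treatment difference is cut by a third. Only the group main effect is.
- That an effect as large as the protocol's minimum clinically important difference would be reported as falling short of it. The 19.9 mm figure describes the instrument, and nothing says that an all-visit difference will be compared with it.
- That Wilks' Lambda cannot be used with multiply imputed data. Pooling is a detail commonly left to the statistical analysis plan, which is not shown.

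**Conclusion.** The point holds as a matter of an unnamed treatment test and avoidable loss of power. The two-thirds ratio for the group main effect is exact, given equal expected baselines. The power loss is conditional on compound symmetry, equal effects at both follow-up visits, f=0.339 at each visit and an assumed correlation. On those terms the literal reading falls below 80% at every correlation tried, at N=90 and at N=78. The interaction reading is also weaker than adjustment of the two-visit mean at each correlation, clearly at 0.3 and 0.5 and barely at 0.7. Keeping baseline as a repeated level is a valid analysis that does not inflate type I error. The weaknesses are a diluted or undefined estimand and inefficiency.

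**What to change.** Take the 4- and 8-week values as outcomes in an ANCOVA or linear mixed model with group, visit, group-by-visit and the baseline value of the same outcome (VAS or KOOS). Name one baseline-adjusted contrast as the test of each hypothesis, for example the mean of weeks 4 and 8. Report the adjusted pairwise differences G1–G2, G1–G3 and G2–G3 with 95% confidence intervals, under the planned Bonferroni correction. Keep the planned multiple imputation: a model fitted only to participants with a post-baseline value would narrow the stated intention-to-treat set.

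The cost is one degree of freedom (86 in place of 87 at N=90) and a change of wording. It needs no new data and no further participants, and it helps under either reading of the present text. It should be settled before any unblinded analysis.

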After taking the baseline information and randomized into 3 groups (G1, G2 & G3). Subjects in G1 will receive needling and real US scanning, and routine exercise training and education of knee care for 4 weeks and once per week while subjects in G2 will receive DN with placebo US scanning, and routine exercise training and education of knee care for 4 weeks and once per week. Subjects in G3 will be measured all the outcomes at the baseline, at the 4-week and 8-week follow-ups. For G1, the US scanning procedure is done with the subject lies on a bed with pillow in a supine position, and with knee joint supported by a towel in an around 30 degrees flexed position (Appendix VI). For G1, the physiotherapist who received special training for US scanning procedure together with the DN intervention in the Hong Kong Polytechnic University will conduct the US scanning. An US machine with high frequency (4-12MHz) linear probe [Proble Model: L12-4 broadband linear array; US Machine: Philips Lumify US system [Koninklijke Philips N.V., Eindhoven, The Netherlands] is used to assess any sign of tendinopathy over the patello-femoral and medial patello-tibial compartments (Sengupta et al., 2006) with following characteristics: mucoid degenerative changes, heterogeneity or thickening of ligaments, osteophytes, meniscus tear, hyaline cartilage thinning in trochlear cartilage defects with reference to the Outcome Measures in Rheumatology (OMERACT) US Task Force on knee OA (Bruyn et al., 2014). To avoid anisotropy, there are two views that should be used included long axis and short axis to confirm pathology (Jacobson, 2018). With integration to detail physical examination, a physical diagnosis will be made. US-guided DN will be applied to the pathological structures e.g. tendinopathy over the patella-femoral and medial patella-tibial compartments. It is a tailor-made treatment and it will last for 15 minutes and the number of needling depending on the subject’s condition. The maximum of sterile needles with the size of Dongbang Acupuncture Needles at 0.3 x 40 mm [Dong Bang Acupuncture, Inc., Marsh Barton, Exeter, United Kingdom] will be seven or below (Chung & Binkley, 2010). The number of needles used will be recorded for analysis. The procedure was performed by the physiotherapist with sterile technique by disinfecting the US probe with a wet towel [Clinell Universal Wipes, GAMA Healthcare Ltd, Hemel Hempstead, Hertfordshire], covered it with a tegaderm[3M; St. Paul, MN, USA], and used Aquasonic sterile transmission gel [Aquasonic sterile transmission gel; Parker Laboratories, INC] for the transmission of US energy to the subject. The subject’s skin will be disinfected with Betadine antiseptic solution [Mundipharma Pharmaceuticals LTD., Nicosia, Cyprus] over the targeted DN sites. Then physiotherapist will use left hand to do the US scanning and right hand will apply the DN to the target location as planned. Based on clinical experience and the procedure of DN on KOA by previous studies (Cotchett et al., 2011; Tabatabaiee et al., 2019), good response has been observed with the following protocol: the needle will be slowly moving in and out of the target muscle or tendon with the goal of eliciting an appropriate response such as a local twitching response (LTR); sensation such as a dull ache, heaviness, distension, or a reproduction of the participant’s symptoms. Then the needling will be manipulated in and out slowly every 5 minutes for 5 times to reproduce the appropriate response, and the whole treatment time will be 15 minutes. After the treatment finished, sterile gauze [A.R. Medicom Inc. (Asia) Ltd, HKSAR, China] will be applied and pressed on the side of DN. Spot tapes sterile non-stick pad [Orison TM, HKSAR, China] will be used to cover the sites received DN. The case in-charged physiotherapist will state with the subject for the whole procedure to ensure safety.

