
For the G2, the subject will also be positioned in a supine position same as G1. Then the physiotherapist (same therapist as in G1) will wash hand and take sterile gloves, and then do the disinfection to the skin in the target DN sites. DN will be applied to the most painful sites. To blind the patients with a placebo US-guide, the physiotherapist will do the procedure of scanning as G1 but with US monitor’s screen, out-of-view from the G2 patient’s vantage point, was turned off to blind the subjects. Then the needling will be manipulated every 5 minutes and the whole treatment time will be 15 minutes. The whole procedure similar as mentioned in G1, but there is no US scanning. After the treatment finished, sterile gauze will be applied and pressed on the side of DN. The physiotherapist will state with the subject for the whole procedure to ensure safety.

For G3, the subjects received only standardized exercise therapy and educational materials related to the care of their knees. The exercise therapy was conducted under the supervision of a registered physiotherapist weekly for 4 sessions. The exercises focused on improving knee mobility, soft tissue flexibility, muscle strength, balance and proprioception. The participants were instructed to continue the exercises at home three times per week for another four weeks.

All the outcomes will be assessed by an independent research assistant.

Details of outcomes assessment

1. The Visual Analogue Scale (VAS) is commonly used in measuring musculoskeletal pain with a 100mm horizontal line anchored with labels on top of it (Appendix 1). The reliability of the VAS for disability is moderate to good (Boonstra et al., 2008) and VAS is the most reliable tool in assessing pain as compared with numerical rating scale (NRS) and verbal rating scale (VRS), with the smallest errors in the measurement of osteoarthritis knee pain (Alghadir et al., 2018). The minimum clinically important difference (MCID) was 19.9 mm (Katz et al., 2015; Tubach et al., 2005).

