2. Knee injury and Osteoarthritis Outcome Score (KOOS)-short form is validated to be used in KOA patients (Lyman et al., 2016). KOOS is a valid, reliable and responsive outcomes measure, and it can improve the validity as compared with WOMAC (Roos et al., 2003). The Chinese translated version of KOOS is a reliable and valid instrument for OAK patients and showed fairly strong association with WOMAC (Cheung, Ngai and Ho., 2016). As WOMAC requires license and cost, KOOS is free to be used, KOOS already has been commonly used as a functional outcomes in most public hospitals in Hong Kong for KOA patients. The KOOS-short form involves three domains including pain, symptoms and quality-of-life (QoL). The score from ‘0’ to ‘4’ indicated none to severe and then the KOOS pain score can be calculated with the following formula:

KOOS-pain= 100 – (mean score of pain domain x 100)/4

The values of KOOS-subscales (symptoms and QoL) can be assessed by the above formula.

1. Evaluation of the Validity of placebo method

This study involves US-guide and stated clearly in the consent form and information sheet provided to very subjects. If one the study group does not provide US-guide, they may know that they are not allocated into the intervention group. To avoid the bias and potential placebo effect from US-guide, it is necessary to blind the subjects during the procedure of US-guide DN. All the subjects in G1 and G2 will receive either real-US-guide or placebo US-guide with US monitor’s screen, out-of-view from the G2 patient’s vantage point, was turned off to blind the subjects.

To ensure it, all the subjects in G1 and G2 will be asked whether they are receiving a real US-guide or a placebo US-guide DN. Is placebo US-guide really effective to service the purpose of blinding the subjects? Then the data will be collected for analysis by Chi-squared test for the nominal data with using SPSS version 23 (IMB, SPSS) and an alpha is set at 0.05.

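### The G2 sham is described both as scanning and as no scanning, and the screen position is fixed for G2 only, so patient blinding between G1 and G2 is left open

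*Protocol*

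**What the plan says.** All of this is in the Protocol, under Methodology.

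- **G1 procedure** (Details of procedure of applying US-guided DN). The probe is disinfected, covered and used with sterile gel, and it is on the knee while the needle goes in: "Then physiotherapist will use left hand to do the US scanning and right hand will apply the DN to the target location as planned". The text does not say where the monitor stands relative to the G1 patient.
- **G2 procedure** (same section). For blinding, "the physiotherapist will do the procedure of scanning as G1 but with US monitor’s screen" off; the screen is "out-of-view from the G2 patient’s vantage point, was turned off to blind the subjects". After one sentence on needle manipulation and treatment time comes: "The whole procedure similar as mentioned in G1, but there is no US scanning". The G2 preparation mentions hand washing, gloves and skin disinfection, but no probe cover or gel.
- **Evaluation of the Validity of placebo method.** Ultrasound guidance is disclosed in the consent form and information sheet, and the protocol warns that subjects given no guidance may realise which arm they are in. The sentence on the screen opens with both arms but again ties its position to G2: "All the subjects in G1 and G2 will receive either real-US-guide or placebo US-guide with US monitor’s screen, out-of-view from the G2 patient’s" vantage point. G1 and G2 subjects are then asked which procedure they are receiving. "Then the data will be collected for analysis by Chi-squared test for the nominal data", with alpha 0.05.

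**The concern.** The two statements about G2 lead to different shams. Under one, the patient feels gel and a moving probe and simply has no image to see. Under the other, no probe need touch the knee, and a patient who has read the information sheet could work out that this is not real guidance. A therapist could follow either statement and claim to be following the protocol. The screen raises a smaller version of the same problem: a G1 patient who sees a live image learns the arm, and nothing in the text prevents that.

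G1 and G2 both receive needling, exercise and education from the same therapist, and G3 receives no needling. Only G1 versus G2 therefore isolates image guidance, which is the question in the stated purpose. Pain on the VAS and function on the KOOS are both rated by the patient, so a blinded assessor does not remove the effect of expectation. If the sham is recognised, expectation is confounded with guidance, and no later analysis can separate the two.

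**Working it through.** **Step 1: compare the texts.** The plan gives no figure on this point, so the main check is of wording.

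| Item | G1 | G2 |
|---|---|---|
| Scanning | Yes, real | As in G1 with screen off; then, two sentences later, none |
| Probe cover and gel | Described | Not mentioned |
| Probe held during needling | Yes, left hand | Not stated |
| Screen on or off | Real imaging | Off |
| Screen out of patient's view | Not stated | Stated twice |

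The first row is a contradiction within one paragraph. The second and third rows do not settle it, because they are silent exactly where the two readings differ. The last row is a gap for G1. It is not a statement that G1 patients see the screen.

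**Step 2: what the planned check can detect.** Inputs: n = 30 per arm (Study subjects) and two-sided alpha 0.05 (Evaluation of the Validity of placebo method). The documents give no expected guess rates, so p1 and p2, the shares guessing *real* in G1 and G2, are assumptions shown over a range.

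Power = Φ[(|p1 − p2| − 1.96·s0) / s1], where s0 = √(2·p̄(1 − p̄)/30), s1 = √((p1(1 − p1) + p2(1 − p2))/30) and p̄ = (p1 + p2)/2.

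Worked case, 70% v 50%:
- p̄ = 0.60 and s0 = √(2 × 0.24/30) = 0.1265
- s1 = √((0.21 + 0.25)/30) = 0.1238
- (0.20 − 1.96 × 0.1265)/0.1238 = −0.387, so power = 0.35

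Worked case, 70% v 30%:
- p̄ = 0.50 and s0 = √(2 × 0.25/30) = 0.1291
- s1 = √((0.21 + 0.21)/30) = 0.1183
- (0.40 − 1.96 × 0.1291)/0.1183 = 1.242, so power = 0.89

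| Assumed *real* guesses, G1 v G2 | Power |
|---|---|
| 60% v 40% | 0.34 |
| 70% v 50% | 0.35 |
| 75% v 50% | 0.52 |
| 65% v 35% | 0.65 |
| 80% v 50% | 0.69 |
| 70% v 30% | 0.89 |
| 90% v 50% | 0.94 |

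Exact enumeration of the uncorrected Pearson test gives the same picture: 0.35 for 70% v 50%, 0.52 for 75% v 50% and 0.69 for 80% v 50%.

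**Step 3: match scenarios to mechanisms.** Rows with G2 at 50% describe leakage confined to G1, such as a visible live image. If G2 patients felt no probe, few of them would guess *real*, and the relevant rows are those like 70% v 30%, where the test has power of about 0.9 or more.

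**The case against.** The strongest defence is that the intention is clear. The flow chart, the G1/G2 summary and the placebo section all speak of a placebo scan or placebo guidance, and the protocol itself names the hazard of omitting guidance. Read that way, the conflicting sentence means only that no real imaging takes place. This is the likelier intention, and it makes the repair one of drafting. It does not remove the point: the sentence does not say this, and the G2 text never puts a probe or gel on the knee.

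Two stronger readings are tempting, and the documents do not support them.

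- *The screen position differs by arm, so the sham reveals allocation.* The protocol specifies the position for G2 and is silent on G1. No text says that G1 patients can see the monitor.
- *The blinding check would probably miss a failed sham.* This holds only for mild leakage. The most serious failure, a G2 session without a probe, would very likely give a significant result. What stands is narrower: a non-significant result with 30 per arm does not show that blinding worked. Nor does the protocol say that it would be read as proof; it poses the question and names a test.

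The choice of blinding index, a *don't know* option and the visit at which the question is asked are details that a statistical analysis plan or case report form may hold. They are not part of this point.

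**Conclusion.** The contradiction on scanning in G2 is real and stands in current text. The position of the G1 screen is an open gap. Together they leave patient blinding of G1 versus G2 dependent on how the therapist reads one paragraph. A reader might infer that the trial is in fact unblinded; the documents support only that it could be, if G2 is done without scanning or if G1 patients can see a live image.

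The bias in VAS or KOOS cannot be sized from the documents. The limits of the check can be, under assumed guess rates: power of about 0.35 at 70% v 50% and about 0.7 at 80% v 50%, against about 0.89 at 70% v 30%. The check can expose a grossly failed sham but cannot repair it, and it cannot certify a good one. The wording should be settled before treatment starts, because a sham delivered inconsistently cannot be corrected in the analysis.

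**What to change.** 1. Reconcile the G2 paragraph to a single sham that serves the protocol's own blinding purpose: covered probe, gel and scanning motions as in G1, including during needling, with no image displayed.
2. Remove the sentence saying that there is no scanning, or reword it to say that no image is displayed or used.
3. State, in both the procedure section and the placebo-validity section, that the monitor is out of the patient's view in G1 and in G2.
4. Secondary: alongside the chi-squared test, report the proportion guessing *real* in each arm with a 95% confidence interval. With 30 per arm and a proportion near 50%, the half-width is about 1.96 × √(0.25/30) = 0.18. The reader then sees how much leakage remains compatible with the data.

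The cost is a few sentences of protocol text, probe cover and gel in G2 sessions if these are not already used, turning the monitor in G1, and one extra line of reporting. No extra visits or patients are needed.

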**Null hypotheses:**

There are two null hypotheses to be tested in this study:

Null hypothesis 1: There would be no significant differences on pain modulation among the subject groups receiving US-guided DN (G1), placebo US-guided DN group (G2) and the control (G3).

Null hypothesis 2: There would be no significant difference on modulation on functional scores among the subject groups receiving US-guided DN (G1) compared to those in the placebo US-guided DN group (G2) or the control group (G3).

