**Outcomes measures:**

Primary outcomes:

1. Pain level of the KOA patients will be assessed by Visual-Analogue Scale (VAS) (Alghadir et al., 2018; Boonstra et al., 2008)
2. The functional mobility of the KOA patients will be assessed by the Knee Injury and Osteoarthritis Outcome Score (KOOS)-short form (Roos et al., 2003; Cheung, Ngai and Ho., 2016)

Secondary outcomes:

1. Compliance of Exercise

Exercise compliance for participants was assessed at 4 weeks and 8 weeks by an independent assessor. The duration of exercise was assessed by hour per week. (Appendix VII).

1. Medication Utilization During the Study Period

The use of pharmacological interventions for participants was assessed at baseline, 4 weeks, and 8 weeks.

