Appendix IV

Data collection form

| Case identity | Date of assessment | Age | Gender | | | BMI | | Unilateral/Bilateral knee pain | | Duration of knee pain | Any injury |
| --- | --- | --- | --- | --- | --- | --- | --- | --- | --- | --- | --- |
|  |  |  | M / F | | | Height: M  Weight: Kg | | R ______  L ______  Both ___ | | ___months | (Y / N) |
| Severity of pain (VAS) | KOOS-Pain score | KOOS-  symptoms  score | KOOS_ADL score | | | Remarks (any any discomfort or side effects): | | | | | |
| _____ mm | ______/36 | ______/28 | ______/68 | | |
|  |  |  |  | | |
| Number of needle used  ( ) | Areas applied dry needling or acupuncture  Oblique/perpendicular insertion: / | | | | |  | Nausea/faint/ hypodermal bleeding others:  _______________________________ | | | | |
| Compliance of exercises: |  | | | | XR: KL scale: Grade 0 / I / II /III /IV | | | | | | |
| Tablets of medication |  | | | Number of tender spots: | | | | | Depth of insertion (mm): | | |
| Ultrasound findings | Patient code: ___________  Real US-dry needling: Y/N  Findings: __Power Doppler of blood flow increased/decreased (neovascularity +/-)  Mucoid degeneration/increased thickness/hypoechogenecicity/hyperechogenecity  __________________________________________________________________________________  __________________________________________________________________________________  __________________________________________________________________________________ | | | | | | | | | | |
| Location of dry needling | [figure not shown]  L medial  R medial | | | | | | | | | | |

Key: Q= quadriceps strength, H= hamstrings strength, ROM=range of motion, R= right and L= left, M=male, F=female, Y= yes and N= no, MMT: manual muscle testing

Scales: mm= minimeter, N=newton, 0 is degree of angle

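### The functional primary outcome is defined only by KOOS pain, symptoms and quality of life, while ADL, the one function-type scale, appears on the data form but is neither declared nor scored.

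*Protocol*

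**What the plan says.** Four places in the protocol bear on this outcome.

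- **Null hypotheses.** Hypothesis 2 reads: "There would be no significant difference on modulation on functional scores among the subject groups". No KOOS subscale is named.
- **Outcomes measures.** The second primary outcome is stated as: "The functional mobility of the KOA patients will be assessed by the Knee Injury and Osteoarthritis Outcome Score (KOOS)-short form".
- **Methodology, details of outcomes assessment, item 2.** The instrument is described thus: "The KOOS-short form involves three domains including pain, symptoms and quality-of-life (QoL"). Items are scored 0 to 4. The scoring rule is "KOOS-pain= 100 – (mean score of pain domain x 100)/4", followed by "The values of KOOS-subscales (symptoms and QoL) can be assessed by the above formula". Nothing else is scored.
- **Appendix IV, data collection form.** The KOOS fields are pain with a maximum of 36, symptoms with a maximum of 28, and "KOOS_ADL score" with a maximum of 68. There is no field for quality of life.

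The questionnaire itself, in Appendix II, is a figure that is not visible in the text available for this review.

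**The concern.** The protocol promises a test of function but defines the instrument by three domains that do not measure function. The form on which results are recorded carries a function-type scale that the outcome text never mentions. A statistician who follows the outcome text would report pain, symptom or quality-of-life scores under the name of function. One who follows the form would report ADL, which has no stated status and no stated scoring.

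Two things are at stake. First, KOOS pain reported as function would largely repeat null hypothesis 1, which already concerns pain and has VAS as its measure. Second, with several candidate scores and none named, the functional result can be picked once the data are known. Either would weaken whatever the trial concludes about function.

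**Working it through.** The plan gives no figure for this outcome to reproduce. The sample size rests on VAS alone ("the effect size of VAS is set as 0.339 for the VAS, power as 0.8, level of statistical significance as 0.05") and is not affected. The check is a comparison of the sections, plus one small piece of arithmetic.

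**Step 1. Declared, scored and collected domains**

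| KOOS score | Declared in outcome text | Scoring given | Field in Appendix IV |
|---|---|---|---|
| Pain | yes | yes | yes, /36 |
| Symptoms | yes | yes | yes, /28 |
| Quality of life | yes | yes | none |
| ADL | no | no | yes, /68 |
| Total, or one named functional score | no | no | none |

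The declared and collected sets share two of three members. They differ on quality of life against ADL. No row is declared, scored, collected and also a function scale.

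**Step 2. Does the wording leave room for a function domain?** The word *including* might suggest that the list is open. It is not: three domains are announced, three are named, and the scoring covers exactly those three.

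**Step 3. Items implied by the form.** With items scored 0 to 4, the number of items is the maximum raw score divided by 4:

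- Pain: 36 / 4 = 9
- Symptoms: 28 / 4 = 7
- ADL: 68 / 4 = 17
- Total: 9 + 7 + 17 = 33

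Thirty-three items for three subscales sit uneasily with the label short form. The outcome text also moves between KOOS and KOOS-short form without saying whether they are the same questionnaire.

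**Step 4. Why the missing ADL scoring matters.** The formula turns a mean item score of 0 into 100 − (0 × 100)/4 = 100, and a mean of 4 into 100 − (4 × 100)/4 = 0. High is therefore good on the 0–100 scale. The form's maxima are those of raw sums, on which high is bad. If the same rule were extended to ADL with all 17 items answered, a raw 34 out of 68 would be a mean of 34/17 = 2 and a score of 100 − (2 × 100)/4 = 50. The protocol does not say that this extension is intended.

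**The case against.** The strongest case on the other side has five parts.

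1. **The hypothesis can be tested.** It speaks of functional scores in general, and the outcome text describes KOOS as a functional outcome in common use in local public hospitals. Pain and symptoms are both defined and collected. This stands in part. A reader might infer that null hypothesis 2 is untestable, but the documents do not support that: tests could be run on the collected scores, and ADL appears to be among them. What is missing is a declared score that represents function.

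2. **Quality of life may still be collected.** A reader might infer that this domain will be entirely missing. The Appendix II questionnaire is not visible and may contain the items. The absence of a field shows only that the form does not provide for the score. This objection stands.

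3. **The form may be the document in error.** Its key explains muscle strength, range of motion and manual muscle testing, for which no field appears, so it looks like an adapted template and ADL could be the stray entry. That is possible, but it does not help. Without ADL, no function-type scale remains anywhere in the visible protocol.

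4. **A long form is not proven.** A reader might infer from the 33 items that the full-length instrument is used. The protocol gives no item count for any version, and short form could mean a subset of subscales. Only the tension with the label can be asserted.

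5. **This is detail for the SAP, and the analysis is blinded.** How many tests the planned Bonferroni correction covers can properly be left to the SAP. A reader might also infer a particular inflation of the family-wise error or loss of power. Such figures would need assumptions that the protocol does not support: no correction, independent subscales of one questionnaire, or a one-way ANOVA in place of the planned mixed-model ANOVA over three time points. They should not be attached. But what a primary outcome measures is not SAP detail when the protocol contradicts itself on it. The plan to analyse blind to group identity reduces the scope for selection without removing it, because coded groups still show which subscale separates them.

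**Conclusion.** The point holds as an internal contradiction about one of the two primary outcomes. The outcome text defines and scores the functional measure only as pain, symptoms and quality of life. The form records pain, symptoms and ADL. No single functional score is named.

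Its size is one subscale of three in mismatch, with pain and symptoms agreeing, and one primary outcome of two left without an identified score. The VAS outcome and the VAS-based sample size are untouched. The conclusion rests on the outcome description and Appendix IV as they stand; the only calculation is the item count, which assumes 0 to 4 scoring for every item on the form, as the outcome text states. It should be settled before unblinding, since the choice of functional score is otherwise open to the results.

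**What to change.** Before unblinding, make the null hypotheses, the list of primary outcomes, the outcome description, Appendix IV and the Appendix II questionnaire agree on one named functional score, with its items and its 0–100 scoring.

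- KOOS-ADL is the natural candidate, because the form already has a field for it. The outcome text would need to declare it and extend the scoring rule to it. The other KOOS subscales would become secondary.
- Either add a quality-of-life field to Appendix IV or remove that domain from the outcome description.
- Correct the short form label so that it matches the questionnaire patients actually complete.

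The cost is a protocol wording change and at most one extra field. The protocol mixes future and past tense, so it is unclear whether data collection had begun. If it has, naming the functional score is more than an editorial change and should be documented, with its date, as made blind to group results.
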